#### Modelled cost-effectiveness analysis

The modelled economic evaluation would investigate the benefits of early diagnosis of CKD cases and the associated prevention/delay of the CKD complications like use of kidney replacement therapies or mortality in the long term. The modelled economic evaluation will include the long-term costs of treatment, regular laboratory investigations, treatment of adverse events, hospital admissions and other relevant costs.

The long-term improved outcomes are hypothesised to translate into a cost reduction and offset the increased costs associated with adding pharmacy-led screening to no screening, for CKD case diagnosis. The modelled economic evaluation will also use published results of long-term observational studies to derive assumptions for the decision analytical modelling and to populate the model. A 5% discount rate will be applied to both costs and benefits.^46^ The uncertainty about results of economic evaluation will be explored using a non-parametric bootstrapping method.

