### Economic evaluation

Health service utilisation will be measured through Medicare and Pharmaceutical Benefits Schemes (MBS and PBS) data linkage, to quantify the symptom-specific and total health service resource use and costs at 12 months, by allocated group. The Consolidated Health Economic Evaluation Reporting Standards guidelines (online supplemental appendix 3) will be followed when reporting the health economic evaluation.^44^

10.1136/bmjopen-2023-079110.supp3Supplementary data

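### The one uncertainty method named for the economic evaluation, a non-parametric bootstrap, cannot by itself carry the uncertainty of the published inputs to the long-term model

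*Protocol article*

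**What the plan says.** The Modelled cost-effectiveness analysis section of the protocol article describes a decision model of the long-term benefit of early diagnosis, including "prevention/delay of the CKD complications like use of kidney replacement therapies or mortality in the long term". On costs, the modelled evaluation "will include the long-term costs of treatment, regular laboratory investigations, treatment of adverse events, hospital admissions and other relevant costs". On sources, it "will also use published results of long-term observational studies to derive assumptions for the decision analytical modelling and to populate the model". The section closes by saying that uncertainty in the economic evaluation will be "explored using a non-parametric bootstrapping method".

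The patient-level resource data have a shorter reach. The Economic evaluation section uses linked claims data "to quantify the symptom-specific and total health service resource use and costs at 12 months, by allocated group".

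No other method for uncertainty in the economic results is named:
- The Within-trial cost-effectiveness analysis section defines the ratio per QALY and gives no uncertainty method of its own.
- The sensitivity analyses in the Data analysis plan concern imputation of missing data.
- Discounting is a single rate with no range: "A 5% discount rate will be applied to both costs and benefits".

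**The concern.** A non-parametric bootstrap measures uncertainty by resampling observed units. For costs and QALYs collected in the trial, those units exist. For long-term progression, kidney replacement therapy, mortality and later costs taken from publications, they do not. Resampling trial participants or pharmacies leaves such an input at the same value in every replicate unless a further step varies it, and the article names no further step.

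Long-term economic benefit is one of the aims under Trial objectives and is repeated under Hypotheses. The modelled section also expects later savings to offset the cost of screening. If the bootstrap were the whole uncertainty analysis, the interval around that claim, or the probability that the service is cost-effective, would reflect the trial's sampling error and leave out the error in the published inputs. Readers would see more certainty than the evidence gives.

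**Working it through.** The document states no interval, standard error or input variance for the economic evaluation, so there is no figure to reproduce. The direction of the effect follows from the method. Its size can only be shown over assumed values.

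**Direction.** Let V_trial be the variance of the modelled result due to trial-derived inputs and V_lit the variance due to published inputs, taken as independent and additive. Then V_total = V_trial + V_lit. A bootstrap of the trial data with published inputs fixed estimates V_trial. Whenever V_lit > 0, that is less than V_total.

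**Size by share of variance.** Let f = V_lit / V_total (assumed).
- Width ratio = √(1 − f)
- True coverage of a nominal 95% interval = 2Φ(1.96 × √(1 − f)) − 1 (normal approximation)

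| f | Width ratio | True coverage |
|---|---|---|
| 0 | 1.00 | 95.0% |
| 0.10 | √0.90 = 0.95 | 93.7% |
| 0.25 | √0.75 = 0.87 | 91.0% |
| 0.50 | √0.50 = 0.71 | 83.4% |
| 0.75 | √0.25 = 0.50 | 67.3% |

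**Size in a toy model.** This ties the trial part to the article's own Sample size section. The modelled benefit is the difference in detection (from the trial) multiplied by the benefit per detected case (from the literature).
- Trial inputs: 10% versus 15% diagnosed; 61 × 30 = 1,830 participants per arm; ICC 0.05.
- Design effect = 1 + (30 − 1) × 0.05 = 2.45.
- Effective number per arm = 1,830 / 2.45 ≈ 747.
- SE of the difference = √[(0.10 × 0.90 + 0.15 × 0.85) / 747] = √(0.2175 / 747) ≈ 0.0171.
- Literature input: gamma-distributed with mean 1 and an assumed coefficient of variation (CV).

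The simulated width of the 2.5th to 97.5th percentile range, bootstrap part alone over full, was:

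| CV of published input | Width ratio |
|---|---|
| 0 | 1.00 |
| 0.1 | 0.95 |
| 0.2 | 0.85 |
| 0.3 | 0.74 |
| 0.5 | 0.56 |

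The narrowing is therefore about 5% when the published input is known precisely and about 44% when its CV is 0.5.

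**The case against.** The strongest reply is that the closing sentence refers to the economic evaluation in general, whereas the same section specifies the modelled evaluation when it means the model. It is the last sentence of the economic block, and the within-trial ratio has no uncertainty method elsewhere. On that reading the bootstrap is mainly meant for the within-trial ratio, where it is appropriate, and probabilistic analysis of the model is detail left to a fuller health-economic plan. The article is brief about the model throughout, and it commits to a health-economic reporting guideline with a supplementary checklist that is not shown.

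Part of this stands. Bootstrapping is right for the within-trial analysis, and a fuller plan may add what is missing. But on either reading the sentence covers the model, because it stands under the modelled heading, directly after the account of how the model is populated. It names a specific method instead of leaving the choice open, and that method cannot do this part of the work alone.

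A reader might infer four stronger claims that the document does not support:
- **That bootstrapping is declared exclusive, with published inputs fixed.** The article says neither. It names one method and is silent on the inputs.
- **That the bootstrap ignores clustering.** An individual-level bootstrap would give an SE for detection of about 1/√2.45 = 64% of the correct one, but the resampling unit is not stated. The Data analysis plan clusters by pharmacy, and the Costs analysis section uses a mixed model.
- **That the model rests mostly on published inputs.** The article gives no weights and says only that published results will be used as well.
- **That the loss of precision is necessarily large.** With precise published inputs it is small.

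**Conclusion.** The point holds in conditional form. The one method named for uncertainty in the economic evaluation fits the within-trial ratio and cannot by itself represent the uncertainty of the model's published inputs. If those inputs are held fixed, the modelled intervals will be too narrow. For any non-zero input variance the direction is certain under independence and additivity.

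The size cannot be determined from the document. The illustrative range, 95% to 50% of full width and about 94% to 67% true coverage, rests on an assumed literature share of 10% to 75% of the variance and on normal errors, which an incremental ratio need not follow.

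The primary outcomes, sample size and trial conduct are unaffected. The point bears on a stated aim and should be corrected before the economic analysis is done.

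**What to change.** In the Modelled cost-effectiveness analysis section, replace the closing sentence with wording to this effect:

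> Uncertainty in trial-derived costs and QALYs will be assessed by a non-parametric bootstrap that resamples the randomised units within arm, respecting the matched pairs where these are used. Uncertainty in the modelled evaluation will be assessed by probabilistic sensitivity analysis. Each literature-derived parameter will be drawn from a distribution based on its published uncertainty, or from a stated plausible range where no standard error is available, jointly with the bootstrap draws. A cost-effectiveness acceptability curve will be reported.

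Name the resampling unit explicitly. The Study setting and design overview calls pharmacies the unit of randomisation, but it also describes groups of co-located pharmacies that share one service model and are allocated in matched pairs. The bootstrap should follow the units actually allocated, meaning the co-located clusters, and keep the pairing where it was used.

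The cost is a few sentences in the plan, the work of assigning distributions to the published inputs, and wider reported intervals. Recruitment and data collection do not change.

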### Patient and public involvement

The study will engage key stakeholders in designing, conducting and reporting the research, as shown in figure 2. Input from consumers and consumer organisations will be actively sought throughout the study implementation. This will be achieved by involving consumers and organisations, such as Kidney Health Australia and the Pharmaceutical Society of Australia, in both the project steering committee and the expert advisory group. Their roles will include contributing to the development of training materials for pharmacists, advising on effective communication and engagement strategies with pharmacists and GPs, and facilitating the implementation and dissemination of research progress and findings via newsletters.

### Ethics and dissemination

The study will be conducted in compliance with the International Conference on Harmonisation Good Clinical Practice guidelines, the World Medical Declaration of Helsinki and all amendments and the Protocol and Protocol Amendments.

The protocol, participant information sheets, consent forms and other relevant case report forms have all been approved by The University of Sydney Human Research Ethics Committee (2022/044). The trial protocol is also registered with the Australian New Zealand Clinical Trials Registry.^47^ The trial registration is provided in online supplemental appendix 4. Study findings will be disseminated in plain language and peer-reviewed forums, including at conferences, via publication in medical journals, and to participants, study staff, clinicians and patient groups, via direct approaches and a variety of traditional and electronic media.

10.1136/bmjopen-2023-079110.supp4Supplementary data

## Discussion

The proposed study presents a protocol for the first large-scale cluster randomised trial to evaluate the effectiveness of community pharmacy-led CKD screening and medication management in improving early disease detection and QUM. The sampling plan primarily targets kidney disease hotspot areas identified by Kidney Health Australia, but also accounts for access to services (ie, metropolitan and rural locations). Within Australia, socio-economic status is lower in rural and remote areas relative to metropolitan areas.^33^ The inclusion of MM2–MM5 locations is also relevant to First Nations communities—these areas overlap much of Inner and Outer Australia where 44% of First Nations people reside.^33 48^ The study is expected to raise awareness among both pharmacists and at-risk individuals about CKD and its risk factors, potentially leading to the early detection of previously unknown CKD cases. Further, by promoting the safe and effective use of medicines, the study findings will potentially lead to reduced adverse drug events and medication-related hospital admissions in people at risk of, or who live with, CKD. Collectively, the study will generate evidence to support the translation of new preventive and public health measures into practice and implement an innovative approach to improving the quality and cost-effectiveness of preventive healthcare intervention.

Effective and sustainable primary care interventions aimed at the early detection and management of CKD have the potential to not only improve health outcomes but also significantly reduce costs associated with extensive hospital services required in later stages, mainly due to the need for regular dialysis or a kidney transplant, which is estimated to cost the Australian economy $A5.7 billion a year.^49^ More importantly, recent modelling has shown that investing in early detection of kidney disease can save the Australian economy about $A10.2 billion over the next 20 years.^49^ Pharmacists are well placed to play a role in the early detection, education and referral of individuals at elevated risk of CKD. By offering screening and QUM services, community pharmacists can contribute to health promotion and education. As integral members of primary healthcare, community pharmacists serve as an important channel for delivering these types of services. Further, their involvement in CKD care contributes towards improving the health status of Australians, including those from lower socioeconomic groups who are disproportionately affected by CKD; increasing public knowledge and awareness of CKD and its risk factors; expanding public health roles for community pharmacists; and enhancing the roles of pharmacists as an integral part of the health workforce. This aligns with Australia’s Primary Healthcare 10-Year Plan, which promotes better utilisation of primary healthcare workforce, including allied health professionals and pharmacists.^50^

There is widespread agreement that an effective programme is needed to support the identification and better management of individuals with early stages of CKD. The subsequent adoption of such a programme, if shown to be successful on a larger scale and in routine practice in Australia, has enormous potential to reduce the population levels of risk and hence reduce preventable healthcare expenditures due to the need for expensive treatments in advanced disease. The adoption of the programme will also enhance the effectiveness of currently remunerated pharmacists’ QUM services such as MedsCheck and Diabetes MedsCheck, which aim to improve patients’ understanding of their medications and ultimately patient outcomes.

By targeting a representative sample of community pharmacies matched by location (rurality) and socioeconomic status,^51^ the study is anticipated to represent a wide range of demographics and regions in Australia. Some of the limitations anticipated during recruitment have been previously described and, while it may not be possible to avoid them fully, we will implement proper incentives to the participating pharmacies, pharmacists and GPs. One major limitation of implementing such programmes is the lack of kidney function information availability, which impacts pharmacist’s ability to identify and intervene in medication-related problems in people with CKD. Using POCT for determining kidney function markers in community pharmacies, the proposed study aims to fill this gap and promote pharmacists’ contributions to CKD care. Finally, the high staff turnover rates and uneven distribution of the pharmacy workforce based on remoteness may affect the recruitment of pharmacists and patients in certain settings, particularly in remote and rural areas.^52 53^

This trial introduces an innovative approach by leveraging existing healthcare resources like My Health Record for a more streamlined referral and medication management purposes. This will improve the utilisation of available resources and maximises their potential. Further, the trial employs an integration-based software system that works with selected pharmacy dispensing systems. This integration is expected to provide a more efficient decision support system for medication review and referral, contributing to improved overall patient care. In addition to exploring community pharmacies’ readiness to incorporate technological solutions to address QUM issues, the study will shed light on potential barriers and enablers to scalability and sustainability of such systems.

In summary, this research presents a unique opportunity for community pharmacists to engage in health promotion and education of people who are at risk of or living with CKD. Given current existing chronic disease services in community pharmacies, our research will incorporate pharmacists in CKD screening and ensure quality medicines use in people who are at risk of or living with CKD. This is in line with the recommended clinical practice guidelines and National Strategic Plan that highlight the importance of early identification and intervention to slow the progression of CKD and occurrence of complications through a multidisciplinary primary care approach.^2 54^
